#### Physical activity intervention (intervention group)

Survivors in the intervention group are asked to add at least 2.5 h of intense physical activities per week. These should include 30 min of strength building exercises and 2 h of aerobic exercises per week. Exercise bouts lasting 20 min or longer are counted towards the total weekly training time. This “dose” of physical activity is based on the international recommendations of healthy physical activities from the Centre of Disease Control and Prevention (CDC; www.cdc.gov) [133].

Based on the initial exercise test, general health status and participant’s preferences and motivation, subjects of the intervention group receive a counselling at the second visit of the baseline assessment (T0b; Fig. 1
**,** Additional file 2: Table S1). A standardized approach is used to assess survivors’ preferences with respect to physical activities, identify possible barriers and determine the individual motivation to start specific activities. Based on this assessment, individualized physical activities are defined and implemented into the participant’s daily life. Survivors of the intervention group are also motivated to incorporate activities of moderate intensities into daily life such as walking instead of driving or climbing stairs instead of taking the escalator. Participants are also advised to reduce inactive behaviour such as television viewing, computer games, etc. with the aim of reducing 25% of their actual media time. The motivational interview is performed by one of the project physiotherapists who have been trained prior to the study.

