#### Compliance

Compliance of the participants is assessed by different means. This will allow us to validate whether the aims of the intervention and control arm have been maintained and to make dose-response analyses for physical activity in this population.

Participants of the intervention group daily report the pedometer steps and sports performed in the web-diary, they are contacted immediately in case of non-compliance, they have monthly telephone contacts with the physiotherapists, and three-to-six-monthly assessment visits with the physicians, physiotherapists and other staff. After the one-year intervention, a structured interview is performed with the participants of the intervention group to assess their opinion on the intervention, their compliance, reasons for compliance or non-compliance and readiness to continue the physical activity programme. Furthermore, at each study visit (3, 6, and 12 months), the retained steps of the pedometers over 2 weeks prior to the visits are (unknown to the participants) downloaded and entered into the study database to assess how accurate participants of the intervention group report their daily steps in the web-diary.

Participants of the intervention and control group report their actual activities at each visit (T3, T6, and T12) and we objectively measure the activity levels at T6 and T12.

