The secondary analyses include several steps: *First*, we will do the same ITT analysis with appropriate means of imputation of missing data for all the secondary outcomes. *Second*, we will perform sensitivity analysis on the primary and all secondary outcomes, including, a) complete data (complete case analysis), i.e. observations with missing information on relevant variables will be dismissed; b) analysis of intermediate effects after 3 and 6 months of intervention; c) dose-response analysis based on the actual physical activities (min of vigorous physical activities per week) or physical performance (VO_2_peak) during the period of interest, independent of the group allocation; and, d) per protocol analysis.

Per protocol analysis will include several analyses based on the actual “treatment” that the participants adhered to (independent of group allocation), first based on the reported compliance and second based on the assumed compliance. In the first analysis based on the *reported compliance*, the following participants will be analysed as being in the “intervention group”: participants randomized into the intervention group who reported in the web-diary to have reached at least 2/3 of the target physical activity (addition of 100 min of moderate to vigorous physical activities [MVPA]); and, participants who were randomized to the control group but reported in the physical activity questionnaires to have increased their physical activity level by more than 30 min of extra MVPA per week during the period of interest. The rest of the participants will be analysed as being a “control”. The second analysis of *reported compliance* will include only the participants sufficiently compliant with the protocol that they were allocated to. It will include those randomized into the intervention group who completed at least 2/3 of training volume (e.g. the addition of 100 min per week of vigorous PA) and compare them to those randomized into the control group with no more than 30 min of extra vigorous PA per week than at baseline during the period of interest.

The analysis on the *assumed compliance* will be done according to the analyses of the reported compliance but with participants being defined as compliant if they reach an increase of ≥5% in VO2peak and/or ≥10% in the ventilatory anaerobic threshold from baseline [135].

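### In the first reported-compliance analysis, the same activity gain between 30 and 100 min/week gets opposite labels depending on the randomised arm

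*Protocol article*

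**What the plan says.** The Data analysis section of the protocol article lists a per-protocol analysis as item d) of the sensitivity analyses on the primary and all secondary outcomes. It says these analyses follow the treatment participants actually adhered to, whatever their allocation.

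The first reported-compliance analysis builds its intervention group from two sources:
- participants randomised to intervention who "reported in the web-diary to have reached at least 2/3 of the target physical activity (addition of 100 min of moderate to vigorous" activity;
- controls by randomisation whose own questionnaire answers show them "to have increased their physical activity level by more than 30 min of extra MVPA per week during the period of interest".

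The remainder clause is "The rest of the participants will be analysed as being a" control. It therefore takes in intervention-arm participants below 100 min.

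The second reported-compliance analysis moves nobody. It compares compliers within their own arm, using the same 100 and 30 min figures, but there in vigorous activity ("e.g. the addition of 100 min per week of vigorous PA").

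The target behind the 100 min is in the Physical activity intervention section: "Survivors in the intervention group are asked to add at least 2.5 h of intense physical activities per week". On measurement, the Compliance section says that both arms report their activity at T3, T6 and T12 and adds "we objectively measure the activity levels at T6 and T12".

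**The concern.** An analysis by exercise received needs one definition of exposure for everyone. Here the definition differs by randomised arm in two ways: the cut-off (100 v 30 min) and the instrument (daily web-diary v questionnaire). A less active control can enter the intervention group while a more active intervention participant is sent to the control group. That contradicts the section's own principle that allocation should not matter.

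The instruments also differ in content. The diary, kept by the intervention group, records strenuous exercise, and only bouts of 20 min or longer count towards training time. The seven-day recall questionnaire covers moderate, hard and very hard activity. The intensity definition also shifts: the target is intense activity, the first analysis counts MVPA and the second counts vigorous activity, with the minute thresholds unchanged.

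At stake is the reading of a sensitivity analysis attached to every outcome. Under the name per protocol it would look like a check on the ITT result, although it reassigns participants and gives up the protection of randomisation.

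**Working it through.** **Inputs from the protocol article.** Target: 2.5 h = 150 min added per week (Physical activity intervention). Intervention-arm rule: at least 2/3 of target, 100 min, web-diary. Control-arm rule: more than 30 min extra per week, questionnaires (both Data analysis). Recruited: 75 per arm (Sample size).

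**Reproducing the plan's figure.** 2/3 × 150 = 100 min, as stated. The control-arm cut-off is 30/150 = 20% of the target and 30/100 = 30% of the intervention-arm cut-off.

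**Applying the rule as written to the same gain x (min/week).**

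| x | Randomised to intervention | Randomised to control |
|---|---|---|
| 0 | control | control |
| 30 | control | control |
| 31 | control | intervention |
| 60 | control | intervention |
| 99 | control | intervention |
| 100 | intervention | intervention |
| 120 | intervention | intervention |

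The labels conflict for 30 < x < 100, a band 100 − 30 = 70 min wide. This step needs no outside assumption. With any single cut-off c applied to one instrument in both arms, the band has width 0, and nobody labelled control can have a larger measured gain than somebody labelled intervention.

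**How many people move (assumed values).** The article gives no distribution of activity gains. Assume normal gains with control mean 0, intervention mean m from 60 to 150, and a common SD s from 40 to 90 min/week.

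- Intervention participants relabelled control = 75 × Φ((100 − m)/s). Highest, m = 60, s = 40: 75 × Φ(1.00) = 75 × 0.841 ≈ 63. Lowest, m = 150, s = 40: 75 × Φ(−1.25) = 75 × 0.106 ≈ 8.
- Controls relabelled intervention = 75 × [1 − Φ(30/s)]. With s = 40: 75 × 0.227 ≈ 17. With s = 90: 75 × 0.369 ≈ 28.
- Of the relabelled intervention participants, those inside the 30–100 band number about 8 (m = 150, s = 40) to 46 (m = 60, s = 40).
- Take one relabelled participant from each arm at random. The one now called control is the more active in about 16% (m = 60, s = 90) to 86% (m = 150, s = 40) of pairs, by simulation.

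**Do the labels still carry information on dose?** Take a further assumed case: intervention mean 80 (SD 60), control mean 10 (SD 40).

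- Labelled intervention: 36.9% of the intervention arm (mean 141.3) and 30.9% of controls (mean 55.6). Pooled mean = (0.369 × 141.3 + 0.309 × 55.6)/(0.369 + 0.309) ≈ 102 min.
- Labelled control: 63.1% of the intervention arm (mean 44.1) and 69.1% of controls (mean −10.4). Pooled mean = (0.631 × 44.1 − 0.691 × 10.4)/(0.631 + 0.691) ≈ 16 min.

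The gap of about 87 min exceeds the 80 − 10 = 70 min between the randomised arms. In about 90% of random pairs taken across the two labels, the person labelled intervention is the more active. So the labels are arm-dependent and noisy, but they still follow dose on average.

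**The case against.** The best defence has four parts.

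- **Consequence is limited.** The primary analysis is ITT in the allocated groups, and this is one variant within one item of a sensitivity list. That stands. Neither the primary inference nor the sample size is affected.
- **The as-treated nature is disclosed.** The text says the analysis follows the treatment actually adhered to. That is fair, but disclosure does not cure a rule that breaks the stated principle, and the name per protocol remains wrong for it.
- **Arm-specific thresholds can be sensible.** They can be, when they only exclude non-compliers within each arm, as in the second analysis. They are not when participants from both arms are pooled under one label.
- **The intensity mismatch is small.** The vigorous-activity figure is introduced as an example. It is a wording point, but it costs nothing to settle together with the rest.

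Three stronger readings are tempting and not supported. A reader might infer that labels are generally reversed; they conflict only between 30 and 100 min/week. A reader might infer that the result says nothing about exercise received; the illustration above shows that mean dose can still separate clearly. And confounding by health or motivation is not peculiar to this analysis: the within-arm compliant analysis also selects on behaviour after randomisation.

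**Conclusion.** The rule is wrong as written, within a defined range. For gains above 30 and below 100 min/week the label is set by the randomised arm, in the opposite direction to what the labels mean, and nothing else in the article repairs this. That follows from the stated thresholds alone. The difference in instrument adds to it by an amount that cannot be estimated, since the article does not say how diary and questionnaire minutes compare.

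The number relabelled (about 8 to 63 of 75 intervention and 17 to 28 of 75 control participants) rests on assumed normal distributions. It should be read as a range of possibilities, not as the size of the error. The point should be corrected before analysis, but it concerns a sensitivity analysis only.

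**What to change.** Choose one of two routes.

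1. Drop the relabelling analysis and keep the within-arm compliant analysis, acknowledging that it too is a selected comparison.
2. Keep an analysis by exercise received, with one cut-off, one intensity definition (MVPA or vigorous, the same across the analyses) and one instrument available in both arms: either self-report at T3, T6 and T12, or accelerometer change from T0 at T6 and T12.

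In either case, call any analysis that reassigns participants as-treated and observational, not per protocol.

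The cost is a few lines of analysis-plan wording and recoding of one variable. Each instrument has a drawback. Accelerometry covers only short windows (at least 7 days) and not month 3, and its T0 wear falls between the two baseline visits, after randomisation. Self-report is subject to recall error.

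A complier-average effect with randomisation as instrument is optional at most. It requires allocation to act only through the defined exercise compliance, which is doubtful because the programme also includes coaching, step counting and a screen-time target. Its interval would also be wide.

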### Primary outcome

The primary outcome of the randomized controlled trial (RCT) is defined as the change in a composite CVD risk score [31, 32] from baseline to 12 months in the participants of the intervention group compared to the participants of the control group. The composite score is based on the assumption that a physical activity intervention shall have overall beneficial effects on the cardio-metabolic risk, affecting most if not all components of the metabolic syndrome. We chose a composite CVD risk score because the prevalence of single components of the metabolic syndrome is low in adolescents and young adults. A longitudinal study showed that a clustered score in adolescents predicted metabolic syndrome in adulthood [33] and was sensitive to change by a physical activity intervention in youth [34]. The composite CVD risk score will be calculated by averaging the z-scores based on gender- and age-specific external references of all components of the metabolic syndrome, including waist circumference, blood pressure, homeostatic model assessment insulin resistance [HOMA-IR], inverted high density lipoprotein cholesterol, triglycerides and cardiorespiratory fitness [32, 34–39].

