### Randomization

To ensure high quality randomization and even distribution of important prognostic factors among the intervention and the control group, a web-based minimization randomization approach (Randomizer: Institute for Medical Informatics, Statistics and Documentation, Medical University of Graz, Austria; available at www.randomizer.at) is used for the 1:1 allocation of participants into the two study arms [43]. We include gender and four categories according to the initial cancer diagnosis (leukaemia and lymphoma; CNS tumours; bone tumours and soft tissue sarcomas; other diagnoses) as grouping variables in the randomization. An external collaborator who is independent of the patient recruitment and enrolment process runs the randomization and treatment allocation (Additional file 2: Table S1).

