#### Sample size

A study by Kriemler and colleagues using the same CVD risk score showed a reduction in the z-score by 14% after a 1-year physical activity intervention in children and adolescents [34]. Our population is older with a history of cancer, intensive treatments and long hospitalisations. We therefore expect higher CVD risk in this population at baseline and even greater changes after an intervention. To be conservative, this study is powered to detect a difference between the intervention and control group of 15% (no change in the control group and 15% change in the intervention group) after the 1-year intervention. For a power of 0.80 and a two-sided type 1 error probability of 0.05, 60 survivors with complete data are required in each study arm. Assuming that 20% of participants will dropout or have missing data, 75 survivors have to be recruited in each arm. From the Swiss Childhood Cancer Registry we identified 4241 eligible 5-year survivors of whom about 1500 were diagnosed and treated in one of the three Swiss Paediatric Oncology Group (SPOG) clinics of initial recruitment (Basel, Lucerne, and Zurich) [3]. Therefore, with an expected participation rate of 20% of the survivors contacted and invited, we will reach a sufficient sample size.

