Model selection Depending on the type of endpoint, mixed linear, logistic, Cox or Poisson regression will be used. All models will include the variables used in the adaptive randomization (age and former cancer diagnosis) and we will test the model assumptions and model fit. The models might be further adjusted for baseline values and important prognostic factors such as sex, socio-economic status, health-behaviours, treatments received, or former treating hospital if we observe an unequal distribution of important confounders between the treatment and control group.

The analysis will be done with Stata Statistical Software version 14 or newer (StataCorp LP, College Station, Texas, USA) and R Statistics (R Core Team, Vienna, Austria, www.R-project.org). A *p*-value <0.05 will be considered as statistically significant. Primary and secondary analyses will be performed when the data collection is finished for all participants.

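### The models' mandatory covariates are given as age and diagnosis, but the minimisation used gender and diagnosis, so gender is only a conditional covariate

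*Protocol article*

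**What the plan says.** The protocol article describes the allocation in its Randomization section. A web-based minimisation procedure "is used for the 1:1 allocation of participants into the two study arms". Its factors are stated plainly: "We include gender and four categories according to the initial cancer diagnosis", used "as grouping variables in the randomization". Age is not mentioned there.

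The model-selection paragraph of the Data analysis section sets the covariates: "All models will include the variables used in the adaptive randomization (age and former cancer diagnosis". It then adds an optional layer: "The models might be further adjusted for baseline values and important prognostic factors such as sex" and several others, to be used "if we observe an unequal distribution of important confounders between the treatment and control group".

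Two other statements affect the size of the problem. The primary score is obtained by "averaging the z-scores based on gender- and age-specific external references", and its change from baseline to 12 months is what is compared. The Secondary outcomes section likewise defines its comparisons as between-group differences in change.

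**The concern.** The two sections describe the same allocation and name different factors, so one of them is wrong. If the Randomization section is right, the analysis paragraph breaks its own rule that every model carries the randomisation variables: it requires a variable that was not minimised on and makes one that was merely optional.

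Reading age as a typing slip for gender does not settle it. The next sentence of the analysis paragraph places sex among the optional covariates, so the paragraph as a whole treats sex as something that need not be in the model.

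The condition for adding sex also works against its inclusion. It depends on seeing an imbalance between arms, and minimisation on gender exists to prevent one.

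When allocation balances a prognostic factor and the model then omits it, the model-based standard error still contains variation that the design has already removed. The p-values become conservative, and precision that the design made available is not used. The covariate set for the primary model is also open to dispute, since diagnosis with age, diagnosis with gender, or all three could each be defended from the text. This is not a detail left to a later analysis plan, because the protocol fixes the list itself.

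**Working it through.** **1. The covariate lists side by side.** No figure in the plan has to be reproduced.

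| | Diagnosis | Gender/sex | Age |
|---|---|---|---|
| Randomization section | factor | factor | not named |
| Data analysis, mandatory covariates | yes | no | yes, labelled a randomisation variable |
| Data analysis, conditional covariates | – | yes, if imbalance is seen | – |

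The lists agree only on diagnosis.

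**2. Standard-error inflation in a linear model.** If sex is balanced by design but omitted, the model-based standard error is too large by about 1/√(1 − R²). Here R² is the share of outcome variance that sex explains beyond the other covariates. The documents give no R², so the values are assumptions:

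- R² = 0: 1.000
- R² = 0.05: 1/√0.95 = 1.026, about 3%
- R² = 0.10: 1/√0.90 = 1.054, about 5%

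**3. Why a low R² is reasonable for changes.** A sex gap that stays constant over time cancels in a change score, however large it is in level. Illustration with assumed values: level variance 1, sex explaining 40% of it, within-sex baseline-to-12-month correlation 0.8.

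- Within-sex variance of change: 2 × 0.6 × (1 − 0.8) = 0.24.
- If the sex gap shifts by 10% over the year, sex contributes 0.10² × 0.40 = 0.004. Then R² = 0.004/0.244 = 1.6%, and inflation is 1/√(1 − 0.016) = 1.008, under 1%.
- If it shifts by 20%, sex contributes 0.20² × 0.40 = 0.016. Then R² = 0.016/0.256 = 6.25%, and inflation is 1/√0.9375 = 1.033, about 3%.

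**4. Simulation of test behaviour.** The sample-size section supplies the frame: "For a power of 0.80 and a two-sided type 1 error probability of 0.05, 60 survivors with complete data are required in each study arm". In a normal approximation this implies a standardised difference of √(2/60) × (1.960 + 0.842) = 0.51. Assumptions not in the documents: 120 completers, biased-coin probability 0.8, diagnosis mix 50/20/15/15%, sexes 50:50. Each scenario had 4000 runs, comparing a model with diagnosis and age against one with diagnosis and sex, at two-sided 0.05.

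| Variance explained by sex | Type I error, sex omitted | Type I error, sex included | Power, sex omitted | Power, sex included |
|---|---|---|---|---|
| 0% | 0.052 | 0.054 | 0.79 | 0.79 |
| 5% | 0.052 | 0.056 | 0.79 | 0.81 |
| 10% | 0.035 | 0.046 | 0.81 | 0.84 |

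The simulation error of a rate near 0.05 is about √(0.05 × 0.95/4000) = 0.003, so the first two rows show no clear difference in type I error. At 10% the test with sex omitted is conservative. Power with sex omitted stays near the planned 0.80; what is lost is the gain that adjustment would have given.

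**5. Would the imbalance condition bring sex in?** The plan gives no threshold for imbalance. Taking 10 percentage points in the sex proportion as a yardstick, no simulated trial exceeded it.

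**The case against.** The strongest reply is that the practical harm is small, and most of that stands. The primary outcome is standardised for gender and age and then differenced, so sex should explain little of it. Several secondary measures are also referenced to norms: VO2peak as percent of predicted, pQCT bone values as z-scores, and SF-36 against age- and sex-stratified norms. The documents do not show that every such reference is sex-specific. Mixed models or baseline adjustment could absorb more of any stable sex difference. Requiring age is harmless in itself; only its label is wrong. It is also fair to say that the documents show a conflict without proving which section is right, since the randomiser's configuration is not shown.

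A reader might infer something stronger in three ways, none of which the documents support.

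- *Sex is left out of every model.* It is a conditional covariate: unlikely to enter, but not excluded.
- *Standard errors are inflated by 12% or 29%.* Those figures need sex to explain 20% or 40% of the analysed variance (1/√0.80 = 1.118; 1/√0.60 = 1.291). Such shares might be thought of for levels of strength or lean mass, but the plan analyses changes and nothing in it supports them there.
- *The result is biased or the false-positive rate is raised.* In the linear models the direction is conservative and the treatment estimate is not biased. The inflation formula does not carry over to the logistic, Cox or Poisson models that the plan also allows. For odds and hazard ratios, the choice of covariates also changes the quantity being estimated, which is a further reason to fix the list in advance.

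The reply does not remove the contradiction in a list that governs all models, including the primary one.

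**Conclusion.** The concern holds as an inconsistency in the specification with a modest statistical cost. As written, a factor named in the Randomization section is missing from the mandatory covariates and would normally stay out, and age is described as a randomisation variable contrary to that section.

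The consequence is conservative model-based inference and some lost precision. It is probably negligible for the primary outcome. For outcomes not standardised by sex, such as handgrip strength or lean mass, standard-error inflation is about 0–5%. That range rests on the assumption that sex explains 0–10% of the variance in change, on near-exact sex balance, and on a linear model. It also takes the Randomization section to describe what was programmed.

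This should be fixed, but it does not threaten the validity of the primary comparison.

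**What to change.** Confirm from the randomiser's configuration which factors were programmed, and make the Randomization and Data analysis sections agree. Do this before unblinding.

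If the Randomization section is right, state that all models include gender and the four-category initial cancer diagnosis as fixed covariates. Remove sex from the conditional list. If age is wanted, list it separately as a prespecified prognostic covariate and do not call it a randomisation variable. If the configuration shows that age was used, correct the Randomization section instead.

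The cost is one sentence and about one model degree of freedom. No data collection or participant is affected.

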#### Data analysis

Descriptive statistics will be used for clinical, sociodemographic and prognostic variables measured at baseline (stratified by intervention and control group). We will use frequencies and proportions with 95% confidence intervals (CI) for categorical variables and mean with ±SD or 95% CI (or median and range) for continuous variables. Descriptive analysis of baseline characteristics will be performed as soon as the baseline assessments are completed for all participants. This cross-sectional analysis will inform about the comparability of the treatment groups and the need for adjustment of between treatment group comparisons. Furthermore, baseline assessments will provide important results about characteristics, health behaviours and health status of long-term CCS in Switzerland. We will also compare the distribution of baseline sociodemographic characteristics to the Swiss Childhood Cancer Registry, to estimate the representativeness of our sample.

The primary analysis will be conducted as intention-to-treat analysis (ITT) for the primary outcome (change in composite CVD score from T0 to T12). All participants will be analysed in the group where they were originally allocated and missing data will be imputed by means of last observation carried forward (LOCF) [134]. LOCF is an appropriate procedure in this setting because it will lead to more conservative effect estimates (i.e. towards the null), because lost to follow-up is more likely to occur in the intervention group (because of an intensive and time-consuming programme) which is the group expected to change (improve). Attempt will be done to follow up all randomised participants, even if they withdraw from the allocated treatment. If the parameters of the composite CVD risk score are skewed, they will be transformed to reach normal distribution for calculating the z-scores.

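### Adjusting the primary model for the baseline score is left to an undefined chance imbalance, which forgoes precision and leaves the covariates open

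*Protocol article*

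**What the plan says.** The Primary outcome section defines the endpoint as the "change in a composite CVD risk score [31, 32] from baseline to 12 months", compared between arms, and Data analysis repeats that the intention-to-treat analysis is of this change.

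The covariate rules are in Data analysis, under Model selection. One group is compulsory: "All models will include the variables used in the adaptive randomization (age and former cancer diagnosis"). The baseline score is not in it. A second group is permissive: "The models might be further adjusted for baseline values and important prognostic factors such as sex", followed by socio-economic status, health behaviours, treatments and treating hospital. That second group applies only "if we observe an unequal distribution of important confounders between the treatment and control group".

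An earlier paragraph of Data analysis shows how the decision is to be made. Baseline characteristics are described by arm once all baseline assessments are complete, and "This cross-sectional analysis will inform about the comparability of the treatment groups and the need for adjustment of between treatment group comparisons".

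No threshold, test or closed list of variables is given for the trigger, and no other section commits the primary model to the baseline score.

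**The concern.** As worded, the default primary model analyses change in the score, adjusted for the randomisation variables but not for the T0 score. The T0 score enters only if someone judges the arms to be unequal.

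That selects covariates on the wrong quantity. After randomisation, a baseline difference between arms is chance and says nothing about how much a covariate explains of the outcome. The baseline value of the outcome itself can be expected to be strongly prognostic before any data are seen.

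Two things are at stake. One is precision that costs nothing, because a change score cannot be computed without the T0 score. The other is that the rule is permissive, undefined and open-ended, so the covariates of the primary model are not fixed in advance.

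**Working it through.** **Inputs.** From Sample size: two-sided α 0.05, power 0.80, 60 per arm with complete data, 20% dropout or missing data. Assumed, because the protocol gives no figure: the correlation ρ between baseline and 12-month scores (range 0.5 to 0.9), equal SDs at both visits, and that the 60 per arm refers to a change score without baseline adjustment.

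**The plan's own figures.** 60 / (1 − 0.20) = 75 per arm, as stated. The 60 itself cannot be reproduced, because the 15% difference comes without an SD. Back-solving, 60 per arm at 80% power implies a standardised difference on the change score of (1.960 + 0.842) × √(2/60) = 0.51.

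**Gain from always adjusting.** With score SD σ and n per arm:
- change score: variance of the difference = (2σ²/n) × 2(1 − ρ)
- adjusted for baseline: (2σ²/n) × (1 − ρ²)
- ratio = (1 + ρ)/2, so the variance saved is (1 − ρ)/2
- power at 60 per arm = Φ(2.802/√((1 + ρ)/2) − 1.960)

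Missing 12-month scores are to be filled by last observation carried forward (LOCF). If 20% carry their baseline score forward (assumption), the correlation becomes 0.2 + 0.8ρ and the saving shrinks to 0.8 × (1 − ρ)/2.

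| ρ (assumed) | Variance ratio | Variance saved | Power at 60 per arm | n per arm for 80% | Variance saved under LOCF |
|---|---|---|---|---|---|
| 0.5 | 0.75 | 25% | 0.90 | 45 | 20% |
| 0.6 | 0.80 | 20% | 0.88 | 48 | 16% |
| 0.7 | 0.85 | 15% | 0.86 | 51 | 12% |
| 0.8 | 0.90 | 10% | 0.84 | 54 | 8% |
| 0.9 | 0.95 | 5% | 0.82 | 57 | 4% |

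**Does the trigger recover the gain?** The protocol defines no trigger, so a mechanical one was simulated: adjust only if the baseline scores differ at p<0.05 (normal data, 60 per arm, 40,000 trials per setting, no other covariates). Powers are slightly below the formula values because t tests were used.

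| ρ | Power, never adjust | Power, triggered | Power, always adjust | Type I error, triggered |
|---|---|---|---|---|
| 0.5 | 0.79 | 0.80 | 0.89 | 0.045 |
| 0.7 | 0.79 | 0.80 | 0.85 | 0.046 |
| 0.8 | 0.79 | 0.80 | 0.83 | 0.048 |
| 0.9 | 0.79 | 0.79 | 0.81 | 0.047 |

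The trigger recovers about a tenth of the gain or less. At ρ = 0.5, for example, it recovers (0.804 − 0.793)/(0.891 − 0.793) = 0.11. A looser trigger at p<0.20 recovers about a quarter to a third (power 0.83, 0.81, 0.81, 0.80). Type I error stays below 0.05 under both.

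**What undefined discretion could do.** If an analyst reported whichever of the two models was significant, type I error would be 0.075, 0.068, 0.066 and 0.058 for the four values of ρ. In trials with a baseline difference at p<0.05, leaving the change score unadjusted gives a conditional type I error of 0.185, 0.127, 0.099 and 0.083; adjusting gives 0.043 to 0.054.

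**The named randomisation variables.** Model selection gives them as age and diagnosis. The Randomization section says minimisation used gender and four diagnosis categories. Sex, an actual minimisation factor, therefore sits in the optional list and falls under the imbalance trigger.

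**The case against.** Several stronger readings are tempting, and the protocol does not support them.

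- *The p-values rest on a hidden look at the data.* The look is announced, with its timing, and concerns baseline data. The Blinding section also plans to blind the statistical analysis to allocation where possible. No outcome-driven choice is shown.
- *Type I error is inflated.* A mechanical trigger is slightly conservative. Inflation needs a choice between models by their results, which nobody plans, although the loose wording does not exclude it.
- *The default is an unadjusted analysis.* It includes the randomisation variables; only the baseline score and further factors are left open.
- *Regression to the mean biases the result.* Under randomisation it affects both arms equally in expectation. It matters only given a chance imbalance, which is the case in which the protocol contemplates adjusting.

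On size, the correlation appears nowhere in the protocol, nor does the model behind the 60 per arm, and LOCF dilutes the gain. The protocol also names mixed linear regression, which, depending on how baseline enters, can match a baseline-adjusted analysis; the article does not say. The loss is therefore conditional.

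Last, a condensed article may leave the final covariate list to an analysis plan. That would answer a silence. Here the article states a rule, and the rule is what needs changing. All these limits stand; they bound the point without removing it.

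**Conclusion.** The point holds as a matter of precision and pre-specification. The stated rule ties baseline adjustment of the primary model to an undefined chance imbalance, when the case for adjusting is known in advance. Under the assumptions above, always adjusting saves 25% to 5% of the variance for ρ from 0.5 to 0.9, about 2 to 10 points of power at 60 per arm, and somewhat less under LOCF. This is a forgone gain. It is neither a bias nor a shortfall against the planned 80%. The wording of the rule is certain; the size is only as firm as the assumed correlation, the equal SDs and the change-score basis for the sample size. The change should be made, but the trial's validity does not hang on it.

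**What to change.** In Data analysis, under Model selection:

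- State that the primary model always includes the baseline composite score and the minimisation factors actually used, regardless of observed balance.
- State that each continuous secondary outcome measured at T0 is adjusted for its own baseline value.
- Delete the imbalance trigger here, and the matching statement earlier in the section that the baseline comparison will inform the need for adjustment. Keep the baseline tables for description only.
- Fix any further covariates in advance, including whether age is kept, or confine them to sensitivity analyses.
- Correct the named randomisation variables to match the Randomization section (gender and diagnosis category).

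The cost is a few sentences, best settled before the analysis is unblinded. No new data or participants are needed.
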